## Statistical considerations

### General design issues

Data will be analyzed using the intention-to-treat approach.

### Sample size and randomization

We did not find any similar study that has evaluated our primary objectives. So, we considered one of the main secondary objectives to estimate the required sample size. Mahmoodpoor and co-workers [35] reported the ICU stay in two study groups as 18.6 ± 8 and 11.6 ± 6.3 days. Considering alpha error of 0.05 and power of 80%, the required sample size allowing for 10% dropout is 20 patients in each group.

### Outcomes

#### Primary outcomes

The primary outcomes are
Energy homeostasis (calorie intake-estimated calorie requirement)Protein catabolism (nitrogen balance)
Nitrogen balance is a measure of the net change in total body protein. It is the difference between nitrogen eliminated from the body and nitrogen ingested in the diet. A positive or neutral nitrogen balance shows that protein stores are increased or maintained, while a negative nitrogen balance indicates protein mass is decreasing. The practical method for estimating nitrogen balance supposes that total nitrogen loss is equal to urinary urea nitrogen excretion plus 4 g/day additional loss from non-urinary urea nitrogen, gastrointestinal, and insensible losses [36, 37]. To measure the nitrogen balance, during the 24-h urine collection, the total intake of protein will be recorded to calculate nitrogen intake: 24-h urine samples will be immediately delivered to the laboratory to measure urea nitrogen.
3.Muscle protein degradation (3-methyl histidine (3MH) in 24-h urine)
3MH is exclusively found in muscle proteins, and after protein degradation, it is rapidly excreted in the urine without further reutilization or metabolization. So, measuring urinary 3MH, after at least 1 day of a meat-free diet, can be used as a biomarker of muscle protein breakdown [38, 39]. After a 1-day meat-free diet, 24-h urine will be collected. Urine samples will be centrifuged for 20 min at 1000×g. The supernatant will be collected and stored at − 70 °C for a maximum of 2 months. The ELISA method will be used for 3MH detection.
4.Muscle protein turnover (3MH/creatinine ratio in 24-h urine)
Since 24-h urinary creatinine estimates the total pool of muscle proteins, muscle protein turnover can be calculated from the 3MH/creatinine excretion ratio [38]. A 24-h urine sample will be delivered to the laboratory to immediately measure creatinine by the enzymatic method.
5.Lipolysis (free glycerol in serum)
Free glycerol is an important index of lipid metabolism. When the body uses stored fat as the energy supply, glycerol and fatty acids are released into the circulation. The absence of glycerol kinase in the adipocyte decreases triacylglycerol resynthesize and supports hepatic gluconeogenesis [40]. After obtaining the overnight fasting blood sample, the serum will be separated. The serum sample will be stored at − 70 °C for further measurement of free glycerol by enzymatic colorimetric method.
6.Glucose homeostasis (fasting blood sugar (FBS), insulin)7.Inflammatory status (CRP, neutrophil/lymphocyte ratio (NLR))
NLR is an available measurable marker used to measure systemic inflammation.
8.Dysbiosis status and luminal integrity (endotoxin levels)
Intestinal gram-negative bacteria are the major source of lipopolysaccharides (LPS), which are referred to as endotoxins. In the case of reduced intestinal barrier integrity due to dysbiosis, luminal endotoxins can enter the circulation [41]. Endotoxin activity assay (EAA) will be used to determine endotoxin levels in whole blood.

#### Secondary outcomes

The secondary outcomes are:
Enteral feeding tolerance (abdominal examination and GRV measurement)Clinical prognosis (APACHE and SOFA score)Nutritional status (NUTRIC score)Infectious complications incidencePressure ulcer incidence and gradeVentilator-dependent daysLength of ICU stayLength of hospital stay28-Day mortality

### Data analysis

Data will be analyzed using SPSS for windows version 11.5 and MedCalc Statistical Software version 18.11.3 (MedCalc Software bvba, Ostend, Belgium; https://www.medcalc.org; 2019). Descriptive (frequency, percentage, mean, standard deviation) and inferential analysis (student *t* test, paired sample *t* test, repeated measures analysis of variance (ANOVA)) will be performed. Any covariates will be controlled by ANCOVA or binary logistic regression. All tests will be two-tailed and a *p* value <0.05 will be considered as statistically significant.

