### Random allocation and blinding

After providing their written consent, patients are randomly allocated in a 1:1 ratio to the intervention or control group (A or B). Patients will be randomized through a stratified sequential randomization plan generated online. Randomization will be stratified by disease severity (Acute Physiology and Chronic Health Evaluation (APACHE) II,^1^ 0–35 and 35–70). For allocation concealment, we will use sealed opaque envelopes; inside each there is a carbon paper and the A or B card. To avoid probable selection bias, we will write the patient’s name on the envelope before opening it. All patients, researchers, and medical staff will be blinded to the allocation to either synbiotic or placebo capsules. An available third party, the secretary of the ICU, will be aware of whether A or B is allocated the synbiotic supplement. In the case of any complication associated with the intervention allocated, the medical staff will refer to the secretary for details.

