### Concomitant interventions

Concomitant interventions will be:
Antibiotics
It is common that patients under critical care receive at least one antibiotic during their ICU stay. On the other hand, it is believed that antibiotics have bacteriostatic or bactericidal effects on both pathogenic and non-pathogenic bacteria. So, it is recommended that probiotic and antibiotic administration be separated by at least 2 h hours [29].
2.Opioids
Considering their analgesic and sedative properties, opioids are widely used in patients under critical care. Opioids are believed to suppress the immune system and delay GI peristalsis [30]. Delayed peristalsis can increase bacterial translocation out of the GI tract [31].
3.H2 receptor blockers
Prevention of GI tract (GIT) stress ulcers, through H2 receptor blockers or proton-pump inhibitors, is common in critical care practice. Increase in GI acidity can cause overgrowth of some pathogenic bacteria [32].
4.Catecholamines
It is believed that the elevated level of catecholamines in patients under critical care, as prescribed exogenously beside endogenous production, can impair the immune system [33].

These drugs are routinely administered in critical care practice, so we will record and consider them as conflicting factors.

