## Study procedures

### Schedule of evaluations

The schedule of evaluations is shown in Table 1.

**Table 1 Tab1:** Schedule of enrollment, intervention, and assessments in accordance with the Standard Protocol Items: Recommendations for Interventional Trials (SPIRIT) guidelines

Study period																	
	Enrollment	Allocation	Post-allocation														Close- out
Time point	Pre- allocation	Pre- intervention	1	2	3	4	5	6	7	8	9	10	11	12	13	14	15
Enrollment																	
Informed consent form	×																
Eligibility	×																
Demographics	×																
Intervention			×	×	×	×	×	×	×	×	×	×	×	×	×	×	
Assessments																	
APACHEII, Modified NUTRIC, SOFA		×								×							×
GCS and vital signs		×	×	×	×	×	×	×	×	×	×	×	×	×	×	×	
Energy homeostasis		×	×	×	×	×	×	×	×	×	×	×	×	×	×	×	×
Abdominal examination		×	×	×	×	×	×	×	×	×	×	×	×	×	×	×	
Fluid balance examination		×	×	×	×	×	×	×	×	×	×	×	×	×	×	×	
GRV																	According to Fig. 3.
Mid-arm circumference		×	×			×			×			×			×		×
Infectious events		×	×	×	×	×	×	×	×	×	×	×	×	×	×	×	×
Pressure ulcer		×	×	×	×	×	×	×	×	×	×	×	×	×	×	×	×
Mg, P, Na, K, Cl		×	×	×	×	×	×	×	×	×	×	×	×	×	×	×	
Glucose		×	×	×	×	×	×	×	×	×	×	×	×	×	×	×	×
Insulin		×															×
AST, ALT,TG, Urea		×				×			×			×			×		
PreAlb		×								×							×
Outcomes		×															×
Concomitant medication		×	×	×	×	×	×	×	×	×	×	×	×	×	×	×	
Adverse events		×	×	×	×	×	×	×	×	×	×	×	×	×	×	×	
Mortality rate																	After 28 days

*Abbreviations*: *ALT* alanine aminotransferase, *AST* aspartate aminotransferase, *APACHE II* Acute Physiology and Chronic Health Evaluation II, *Cl* chloride, *Cr* creatinine, *GCS* Glasgow coma scale, *GRV* gastric residual volume, *K* potassium, *Mg* magnesium, *Na* sodium, *NUTRIC* Nutrition Risk in Critically Ill, *P* phosphorus, PreAlb pre-albumin, *SOFA* sequential organ failure assessment, *TG* triglyceride

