### Description of evaluations

As shown in Fig. 2, calorie achievement goals are set according to the patients’ modified NUTRIC score. In everyday visits, we will evaluate GI signs and symptoms (e.g. vomiting, diarrhea, abdominal distention) and gastric residual volume (GRV). If there is no sign or symptom of intolerance and GRV is less than 250 ml, EN will be increased by 10%. Otherwise, we will approach as shown in Fig. 3. Energy homeostasis (calorie intake-estimated calorie requirement) will be recorded each day. Mid-arm circumference, which is an available anthropometric measurement tool, will be evaluated twice a week. As all patients receiving EN should be monitored for some clinical and laboratory variables, we set our monitoring approach as reported by Berger MM, et al. [34], Monitoring nutrition in the ICU, Clinical Nutrition (2018). Concomitant medications, pressure ulcers, infectious complications, and other adverse events will be recorded every day. The APACHE II and Sequential Organ Failure Assessment (SOFA) will be scored on days 0, 8, and 15. Before and after the intervention, fasting blood and 24-h urine samples will be obtained. Urine urea nitrogen, 3-Methyl histidine, and creatinine will be measured in urine samples. Fasting blood glucose, insulin, C-reactive protein (CRP) and endotoxins will be measured in fasting blood samples.

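### The analysis section does not commit to adjusting for baseline value or APACHE II, lists within-arm paired tests, and leaves room to adjust for drugs given after randomisation

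*Protocol article*

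**What the plan says.** - **Tests.** The Data analysis section of the protocol article states that "inferential analysis (student *t* test, paired sample *t* test, repeated measures analysis of variance (ANOVA)) will be performed".
- **Covariates.** The next sentence reads: "Any covariates will be controlled by ANCOVA or binary logistic regression". No covariate is named there.
- **Baselines.** Under Description of evaluations: "Before and after the intervention, fasting blood and 24-h urine samples will be obtained". Table 1 also has pre-intervention entries for energy homeostasis and for the severity scores.
- **Stratification.** Under Random allocation and blinding: "Randomization will be stratified by disease severity", with APACHE II bands of 0–35 and 35–70.
- **Concomitant drugs.** After listing antibiotics, opioids, acid suppressants and catecholamines, the Concomitant interventions section says: "These drugs are routinely administered in critical care practice, so we will record and consider them as conflicting factors". On antibiotics it notes: "It is common that patients under critical care receive at least one antibiotic during their ICU stay".
- **Timing of drug data.** Under Description of evaluations: "Concomitant medications, pressure ulcers, infectious complications, and other adverse events will be recorded every day". The Table 1 row "Concomitant medication" is marked once before the intervention and on each of days 1 to 14.

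**The concern.** Three features of the analysis text work against a clean estimate of the randomised effect in a 40-patient trial.

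First, baseline values and a severity score are collected, and severity is used to stratify allocation. The text nevertheless does not commit to using either in the between-arm comparison, so precision that costs nothing may be lost.

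Second, a paired t test compares an arm with itself. ICU patients change over 14 days whatever they receive, so a significant change in one arm and not in the other says little about the product.

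Third, the only factors the article singles out for consideration are drugs whose use is recorded mostly after allocation. The Discussion expects the product to lower infections and improve prognosis. Antibiotic and catecholamine use plausibly follows infection and severity, so it may itself be a result of treatment. Adjusting for it would remove part of the effect. It could also add selection bias, because unmeasured severity drives both drug use and outcome.

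**Working it through.** **1. The plan's own figure.** The Sample size section uses ICU stay, 18.6 ± 8 against 11.6 ± 6.3 days, two-sided alpha 0.05, power 80% and 10% dropout.
- Difference = 7. Pooled SD = √((8² + 6.3²)/2) = 7.20.
- The normal approximation gives 17 per arm, and 17/0.9 rounds up to 19. The t distribution gives 17.6, so 18 per arm, and 18/0.9 = 20.
- The stated 20 per arm is reproduced. Nothing below changes it.

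**2. Precision from the baseline value.** The article gives no correlation r between baseline and final value, so 0.3, 0.5 and 0.7 are assumed. Variance of the treatment effect relative to a t test on final values:
- ANCOVA: 1 − r²
- Change score (the group-by-time test of a two-time-point repeated measures ANOVA): 2(1 − r)
- ANCOVA relative to change score: (1 − r²)/(2(1 − r)) = (1 + r)/2

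| r | ANCOVA vs final value | Change score vs final value | ANCOVA vs change score |
|---|---|---|---|
| 0.3 | 0.91 | 1.40 | 0.65 |
| 0.5 | 0.75 | 1.00 | 0.75 |
| 0.7 | 0.51 | 0.60 | 0.85 |

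Take 18 evaluable patients per arm and an effect of 0.96 SD, for which the final-value t test has 80% power. ANCOVA then has about 84%, 90% and 97.5% power, and the change score about 66%, 80% and 95%. To match ANCOVA, the final-value t test would need 18/(1 − r²), or about 20, 24 and 35 per arm.

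**3. Paired tests.** Suppose both arms change identically and each paired test has power p to detect that change. The chance that exactly one arm is significant is 2p(1 − p):
- p = 0.3: 2 × 0.3 × 0.7 = 42%
- p = 0.5: 2 × 0.5 × 0.5 = 50%, the maximum
- p = 0.8: 2 × 0.8 × 0.2 = 32%

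There is no treatment difference in any of these cases.

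**4. Adjusting for on-treatment drugs.** Of the 15 medication recordings in Table 1, 14 follow allocation. All coefficients in this illustration are assumed. Drug use M = a·T + c·U + error, and outcome Y = −0.3·T + 0.5·M + 0.5·U + error. T is arm, U is unmeasured severity, and U and the errors have variance 1.
- Total effect of treatment = −0.3 + 0.5a.
- Effect after adjusting for M = −0.3 − 0.5·a·c/(c² + 1).

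| Setting | Total effect | Adjusted for drug use |
|---|---|---|
| Treatment lowers drug use (a = −0.5), severity does not drive it (c = 0) | −0.55 | −0.30 |
| Treatment lowers drug use (a = −0.5), severity also drives it (c = 0.5) | −0.55 | −0.20 |
| Treatment does not affect drug use (a = 0, c = 0.5) | −0.30 | −0.30 |

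A simulation of the same model gives these values to within 0.002. In the second row, adding severity to the model would bring the estimate back only to the direct effect of −0.30, not to the total of −0.55.

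**5. Strata.** Bands of 0–35 and 35–70 share the value 35. Every other score belongs to exactly one band.

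**The case against.** The strongest reply is that the text rules nothing out.

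- **Baselines.** The covariate sentence offers ANCOVA, which can carry the baseline value, and repeated measures ANOVA also uses it. A reader might infer that the baselines are wasted. The document does not support that: it fails to commit to baseline adjustment but does not exclude it. Against a change-score comparison the gain is also smaller at high correlation, with a variance ratio of 0.85 at r = 0.7 rather than 0.51.
- **Drugs.** A reader might infer that the plan names on-treatment drugs as model covariates. It does not. The Data analysis section names none, and one medication recording precedes the intervention, so baseline drug use is a possible reading. The covariate list may sit in an analysis plan that is not shown.
- **Paired tests.** They are only listed, beside between-arm tests. Nothing says a treatment claim will rest on them.
- **Strata.** A reader might conclude that the stratification factor is unusable. Only a score of exactly 35 is ambiguous.

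These points stand and limit the strength of the finding. They do not remove it. The article singles out a set of mostly post-allocation exposures for consideration, offers adjustment for any covariate, and sets no limit to pre-randomisation values. It also lists paired tests among the inferential analyses without saying what they may be used for.

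**Conclusion.** The point holds as a weakness in what the plan commits to and permits, not as proof that an invalid analysis has been fixed.

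- A between-arm ANCOVA on baseline value and APACHE II is the better main analysis and uses data already collected. How much it gains depends on an assumed correlation. At r from 0.3 to 0.7 its variance is 0.91 to 0.51 of a final-value t test and 0.65 to 0.85 of a change-score test.
- Paired t tests do not estimate the treatment effect. With identical arms they can disagree in 32% to 50% of trials at within-arm power of 30% to 80%.
- That on-treatment drug use would enter the models is the natural reading of two sections together, not an explicit statement. The resulting bias is conditional: it is absent if treatment does not change drug use, and its size in the illustration rests on assumed coefficients. The condition is, however, a plausible consequence of the trial's own expectation of fewer infections.
- The overlap at 35 is a separate and minor error in the allocation rule.

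**What to change.** Before unblinding, state the following:

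1. For continuous outcomes with a baseline measurement, the main between-arm analysis is an ANCOVA, or the mixed-model equivalent for repeated measurements, on arm, the baseline value of that outcome and baseline APACHE II.
2. ICU stay, hospital stay and ventilator days have no baseline value. For these, adjust for baseline APACHE II only.
3. Covariates in any model, logistic models included, are limited to variables measured before randomisation.
4. Use of antibiotics, opioids, acid suppressants and catecholamines during treatment is reported by arm, descriptively.
5. No treatment claim rests on a paired t test.
6. The APACHE II strata do not overlap, and the text says which one holds a score of 35. Entering APACHE II as a continuous covariate does not settle this, because it does not tell staff which stratum to allocate from. As recruitment had already begun, also record how any such patient was handled.

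The cost is wording. No new data or patients are needed. The adjusted model uses one or two degrees of freedom: with 40 patients, the residual falls from 38 for a t test to 36 with both covariates.

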## Study objectives

### Primary objective

The primary objective is to evaluate the effects of synbiotic supplementation on energy and macronutrient homeostasis and muscle wasting in patients under critical care.

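### Ten measures in eight co-equal primary outcomes are each tested at 0.05, so if any one significant result supports the primary objective, the false-positive chance is roughly 20% to 40%, not 5%

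*Protocol article*

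**What the plan says.** The Primary outcomes section of the protocol article numbers eight outcomes, from "Energy homeostasis (calorie intake-estimated calorie requirement" to "Dysbiosis status and luminal integrity (endotoxin levels". Between them stand nitrogen balance, "Muscle protein degradation (3-methyl histidine (3MH) in 24-h urine", "Muscle protein turnover (3MH/creatinine ratio in 24-h urine", free glycerol, glucose homeostasis (fasting glucose and insulin) and inflammatory status (CRP and NLR). None is marked as leading.

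The primary objective is to "evaluate the effects of synbiotic supplementation on energy and macronutrient homeostasis and muscle wasting in patients under critical care".

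The Data analysis section lists t tests, paired t tests and repeated measures ANOVA, with ANCOVA or logistic regression for covariates. It does not assign them to outcomes. It then states "All tests will be two-tailed" and that a p "value <0.05 will be considered as statistically significant".

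The sample size section does not identify a lead primary outcome either. It rests on length of ICU stay, which the article lists as secondary.

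**The concern.** The primary objective is a single broad statement, and ten separate tests can each be offered in its support. The article does not say whether one, several or all of them must be significant. A reader who sees one primary p value below 0.05 would take it as a finding at the 5% level, but that level applies to a single test and not to the best of ten.

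Three of the ten measures (CRP, NLR and endotoxin) are not named in the primary objective. A lone significant result on one of these would count as a significant primary outcome without directly addressing energy, macronutrients or muscle.

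What is at stake is the trial's central claim. Once results are known, a lead outcome or an adjustment can no longer be chosen credibly.

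**Working it through.** **The plan's own figure.** The article states no familywise error rate. Its one checkable figure is 20 patients per group, from ICU stays of 18.6 (SD 8) and 11.6 (SD 6.3) days, alpha 0.05, power 80% and 10% dropout.
- Difference 7.0; pooled SD = √((8² + 6.3²)/2) = 7.20; standardised difference 7.0/7.20 = 0.97.
- The t-based sample size is 17.6, so 18 per group; 18/0.9 = 20. The figure reproduces and is not in dispute. It gives about 18 evaluable patients per arm.

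**Count of measures (Primary outcomes section).** Energy balance, nitrogen balance, 3MH, 3MH/creatinine, free glycerol, fasting glucose, insulin, CRP, NLR and endotoxin: ten measures in eight outcomes.

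**Chance of at least one p < 0.05 when no measure is affected.** One two-sided between-group test is counted per measure.
- Independent tests: 1 − 0.95^k. For k = 8 this is 0.337; for k = 10 it is 0.401.
- Common correlation ρ: 1 − ∫ φ(u) [Φ((1.96 − √ρ·u)/√(1−ρ)) − Φ((−1.96 − √ρ·u)/√(1−ρ))]^k du, integrated numerically. The article gives no ρ, so the values are assumptions.

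| Assumed correlation | 8 tests | 10 tests |
|---|---|---|
| 0 | 33.7% | 40.1% |
| 0.3 | 30.0% | 35.1% |
| 0.5 | 25.0% | 28.7% |
| 0.7 | 19.1% | 21.3% |

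**Unequal correlation.** Some pairs clearly overlap: 3MH is the numerator of 3MH/creatinine, and energy and nitrogen balance both depend on the same feed. In a simulation of ten measures, the two 3MH measures were given correlation 0.7, and energy with nitrogen balance, glucose with insulin, and CRP with NLR were given 0.5 (all assumed). The chance was 38% with all other correlations at 0, 37% at 0.1, 36% at 0.2 and 34% at 0.3.

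**What adjustment costs.** The standardised difference detectable with 80% power and 18 per arm is (z₁₋α/₂ + 0.842) × √(2/18), by normal approximation.
- α = 0.05: (1.960 + 0.842)/3 = 0.93.
- First Holm step for ten measures, 0.05/10 = 0.005: (2.807 + 0.842)/3 = 1.22.
- First Holm step for seven measures, 0.05/7 = 0.0071: (2.690 + 0.842)/3 = 1.18.

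At the standardised difference of 0.97 used for sizing, power is 83% at 0.05, 59% at 0.0071 and 54% at 0.005.

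**The case against.** Four arguments can be made for the plan.

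**No success rule is stated.** The article nowhere says that one significant primary outcome makes the trial positive, and it ties each measure to its own construct. If each were reported only as a claim about that construct, 5% per claim would hold. This stands as a condition on the figures. It does not remove the concern, because the objective covers the constructs jointly and nothing in the article prevents the any-one-of-ten reading.

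**The detail may be in the analysis plan.** The article is condensed and the analysis plan is not shown. A testing order is often left to that document, so its absence alone would be no finding. Here, however, the article does state a rule: one unadjusted threshold for all tests, with eight outcomes of equal rank. An analysis plan that adjusted would have to override that text.

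**Independence is unrealistic.** This is correct: 40% is a ceiling. Yet even at a common correlation of 0.7 the chance is about four times 5%.

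**The inflammation and endotoxin outcomes fit the rationale.** A reader might infer that CRP, NLR and endotoxin have no connection with the primary objective. The documents do not support that. The study rationale starts from dysbiosis, and the background links inflammation and microbial products to muscle atrophy. What holds is narrower: the objective does not name them.

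**Conclusion.** The point holds. Followed as written, the plan gives a familywise error several times 5% across its primary measures: 21% to 40% for ten tests and 19% to 34% for eight, over assumed common correlations from 0.7 down to 0. Three assumptions carry these figures: any one significant primary result is read as support for the objective, no measure is affected by treatment, and one between-group test is made per measure. The paired tests, repeated measures ANOVA and covariate-adjusted analyses that the plan also lists would add further chances if used for the same claims.

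A reader might quote 29% to 40% as the error rate of this trial. The documents do not support that as a fixed figure: it covers ten measures with correlations of 0 to 0.5 only, and the article gives no correlation at all. The direction of the error does not depend on that choice; the exact size does.

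**What to change.** Before unblinding:
1. Define one between-group, end-of-treatment test for each primary measure, for example ANCOVA adjusted for the baseline value. The schedule collects outcomes before and after the intervention, and the Data analysis section already allows ANCOVA. Energy balance is recorded daily, so the value to be tested must be named. Holm's procedure is undefined without one p value per measure.
2. Apply Holm's procedure across the ten primary measures at two-sided familywise 0.05. This holds under any correlation.
3. State that a primary claim requires a Holm-adjusted p below 0.05, and label all other p values exploratory.

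Moving CRP, NLR and endotoxin to secondary is optional. It would raise the first Holm step from 0.005 to 0.0071. The Trial status section shows that recruitment had already begun, so this would change the primary outcomes of a running trial and must be documented as a dated amendment made before unblinding.

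No new data are needed. The price is the power loss shown in the working: at the first Holm step the detectable standardised difference rises from 0.93 to about 1.22 with ten measures, or 1.18 with seven. Naming a single lead outcome at 0.05 would also hold the error at 5% without a stricter threshold, but only that outcome could then carry the primary claim.
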